## Abstract

**Background:**

Chronic heart failure, is increasing due to the aging population and improvements in heart disease detection and management. The prevalence is estimated at ~10% of the French general practice patient population over 59 years old. The primary objective of this study is to improve the quality of life for heart failure patients though a complex intervention involving patient and general practitioner (GP) education in primary care.

**Methods:**

A randomised, cluster controlled trial, stratified over 4 areas of the Auvergne region in France comparing intervention and control groups. The inclusion criteria are: patients older than 50 years with New York Heart Association (NYHA) stage I, II, or III heart failure, with reduced ejection fraction or with preserved ejection fraction. Heart failure should be confirmed by the patient’s cardiologist according to the European Society of Cardiology guidelines criteria. The exclusion criteria include: severe cognitive disorders, living in an institution, participating in another clinical trial, having NYHA stage IV heart failure, or a lack of French language skills. The complex intervention consists of training at the GP practice with an interactive 2-day workshop to provide a patient’s education programme. GPs are trained to perform case management, lifestyle counselling and motivational interviewing, to educate patients on the main topics including clinical alarm signs, physical activity, diet and cardiovascular risk factors. The patients’ education sessions are scheduled at 1, 4, 7, 10, 13 and 19 months following the start of the trial. The primary outcome to be assessed is the impact on the quality of life as determined using two questionnaires: the Minnesota Living with Heart Failure Questionnaire and SF-36. To detect a difference in the mean quality of life at 19 months, we anticipate studying a minimum of 400 patients from 80 GPs.

**Discussion:**

This trial will provide insight into the effectiveness of a complex intervention to educate patients with heart failure including a 2-day GP workshop and patients’ education programme in the setting of a GP consultation to improve the quality of life in patients with chronic heart failure. This complex intervention tool could be used during initial and further medical training.

**Trial registration:**

ETIC is a cluster-randomised, controlled trial registered on ClinicalTrials.gov [NCT01065142, 2010, Feb 8] and the French drug agency [Agence Nationale de Sécurité du Médicament et des produits de santé; registration number: 2009-A01142-55, on March 5th, 2010].

**Electronic supplementary material:**

The online version of this article (doi:10.1186/s12875-014-0208-3) contains supplementary material, which is available to authorized users.

## Background

Chronic heart failure (CHF) is a common pathology increasing in prevalence due to the aging of the population and detection and improvements in heart disease management [1]. Approximately 10% of the French general practice patient population over 59 years old [2] has CHF. Patients with CHF have poor quality of life due to their symptoms and recurrent hospitalisations, and due to its high complication rates CHF is expensive to treat [3]. Every year in France there are approximately 200 000 hospitalisations due to CHF which accounts for 1.5% of global health expenditure [4]. The European Society of Cardiology guidelines recommend pharmacological therapy to reduce morbidity, mortality and improve patient quality of life; and non-pharmacological management (self-care, behavioural and patient education) to improve adherence to treatment and quality of life [5].

The results from a meta-analysis have shown that the implementation of comprehensive disease management programmes leads to a significant reduction in mortality (odds-ratio (OR) = 0.80), reduced hospitalisation for cardiac failure (OR = 0.76) and all illnesses (OR = 0.58) [6]. In France, some studies have assessed the impact of education for patients with CHF [7,8]. The interventions were delivered by multidisciplinary teams, including outpatient clinics attached to hospitals, which does not reflect the French primary care setting where most general practitioners (GPs) work single-handed. There have been very few studies exclusively focused on assessing the effect of CHF management programmes in a primary care setting, but several including primary care situations amongst others [9-13]. Other studies have been conducted in primary care but the interventions were not carried out by the GPs themselves: i.e. patient recruitment occurred in primary care but the intervention was conducted by nurses or doctors’ assistants [14,15]. More evidence is needed in primary care because the generalisability of hospital- or outpatient-based programmes to primary care is limited.

Therefore we want to assess the effectiveness of a complex intervention that incorporates education of patients with CHF by GP’s trained to promote self-care management and behaviour management. The aim of the ETIC trial (Education Thérapeutique des patients Insuffisants Cardiaques/Therapeutic Education for patients with Cardiac Failure) is to improve the quality of life of patients with heart failure though a complex intervention involving patient and GP education in primary care. The secondary objectives are to assess the effects of the training on: all-cause and heart-failure (HF)-associated mortality; all-cause and HF-associated hospitalisation; the cumulative number of all cause death and HF hospitalisations; adherence to treatment; changes in NYHA heart failure stage; changes weight and body mass index (BMI) and treatment for a follow-up period of 19 months.

## Methods

### Study design and randomisation

The global study design is presented in Figure 1. ETIC is a cluster-randomised, controlled clinical trial with general practices as the unit of randomisation (Figure 2). The randomisation list was drawn up with the software Stata, version 10 (StataCorp, College Station, Texas, US) by the biostatistician before the start of the trial. A cluster design was chosen for pragmatic reasons and to avoid contamination bias. All GPs who volunteered were randomised and the patients did not know to which group their GP had been assigned. GPs that were located within the same practice represented a cluster and such GPs were placed in the same group to avoid cross-contamination. The trial is being carried out across the Auvergne in France, with stratification according to the 4 departments (administrative areas) in this region.

**Figure 1 Fig1:**
[figure not shown]
**Overview of ETIC study protocol.**

**Figure 2 Fig2:**
[figure not shown]
**ETIC trial flow chart.**

### Inclusion and exclusion criteria

#### Inclusion criteria

Patients older >50 years, with New York Heart Association (NYHA) stage I, II or III CHF with reduced ejection fraction (HFrEF) or preserved ejection fraction (HFpEF) are eligible for inclusion. Heart failure has to be documented and confirmed by the patient’s cardiologist according to the European Society of Cardiology guidelines, namely, patients have, currently or in the past, symptoms, signs of fluid retention and objective evidence of an abnormality of the structure or function of the heart at rest confirmed by echocardiographic criteria [5]. When GPs recruit patients, patients’ cardiologists are sent a letter to ask them to confirm heart failure according these guidelines.

#### Exclusion criteria

Patients that suffer from severe cognitive disorders (as judged by the GP), who are living in an institution at the time of inclusion, are participating in another clinical trial, have NYHA stage IV heart failure, or a lack of French language skills are excluded from participating in the trial.

### Instruments and outcomes

The primary outcome is the patients’ quality of life as measured by SF-36 [16] and the Minnesota Living with Heart Failure Questionnaire (MLHFQ) [17]. The SF-36 is a generic measure of health impairment, with scores ranging from 0 to 100: zero indicates the worst quality of life and 100 the best. The MLHFQ is specific for chronic heart failure and has 21 questions with scores ranging from 0 to 105: zero indicates best quality of life and 105 the worst. Quality of life is assessed at baseline and at 7, 13 and 19 months by the patients, or their main caregiver, within 7 days of their appointment with their GP. A score of < 24 on the MLHFQ signifies a good quality of life, a score between 24 and 45 signifies a moderate quality of life, and a score > 45 signifies a poor quality of life [18]. We will assess these cut-off scores to interpret results in clinical terms. We were unable to find published cut-off information for the SF-36 health scores.

The secondary outcomes are: all-cause and heart-failure-associated mortality; all-cause and heart-failure-associated hospitalization, number of days in hospital; the cumulative number of all cause death or HF hospitalizations and the cumulative number of days of hospitalisation; adherence with therapy; evolution of NYHA heart failure stage; evolution of treatment; and changes in weight and body mass index (BMI) at 19 months. We will assess guideline adherence of treatment at baseline and during the follow-up period. Patient adherence with therapy will be assessed by the patients themselves with a self-administrated questionnaire (validated in French) at baseline and at the end of follow-up period [19].

Should the planned follow-up appointment be missed, the reason is identified and categorised as follows: lost-to-follow-up; death; unable to attend for another reason. Hospitalisations and mortality will be recorded by GPs at each planned visiting case report form.

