#### Statistical analysis

The statistician will be blinded with regard to treatment allocation. The responses to the questionnaire will be entered into a customised Access database (Microsoft, Redmond, Wash, US). Analyses will be made using Stata, version 13 (StataCorp, College Station, Tex, US). If necessary, an adjustment to accommodate differences between the baseline characteristics of the groups will be made. Continuous data will be presented as mean ± standard deviation (SD). The comparisons between study groups will be analysed using Chi-square or Fisher's exact test for categorical variables, and Student's or Mann–Whitney tests for quantitative variables, with normality verified by the Shapiro-Wilk test and homoscedasticity by the Fisher-Snedecor test. The correlation between SF-36 and MLHFQ will be assessed using Pearson’s correlation coefficient. Hierarchical linear regression models with random-effects levels for practice, individuals within practices and repeated measurements per individual (slope and intercept) will be used to estimate the effects of the intervention on SF-36 and MLHFQ scores for the post-baseline time points. These models will include an interaction factor between both the randomisation group and the particular time point, and will be adjusted for baseline SF-36 scores, age, gender, diagnosis, smoking history, treatment and socioeconomic status. Intra-class correlation coefficients will be presented by group. The secondary analyses will compare deaths (overall and due to heart failure) using Kaplan-Meier estimation and the Cox proportional-hazards regression model, hospitalisations (overall and due to heart failure), NYHA stage, treatment, adherence, weight and obesity between the groups with longitudinal random-effects models described previously. Estimation methods developed by Verbeke and Molenberghs will be used to account for missing data (GPs and patients) [25].

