For instance, one study on 240 patients with a mean age of 70 years and a majority of NYHA stage III (96.4%) reported baseline SF-36 mean scores of 45.1 in the intervention group and 46.8 in the control group [14]. The baseline MLHFQ mean scores were 42.5 and 42.6, respectively. In another study on 200 patients with a mean age of 63.5 years and a majority of patients with NYHA stage II-III (94%; 6% had stage IV), the baseline MLHFQ mean scores were 64.3 and 62.4 in the intervention and control groups, respectively [10]. In a study comparing home and hospital follow-up in 280 patients with a mean age of 71 years and slightly fewer patients with NYHA stage II-III (85%; 15% had stage IV), the baseline MLHFQ scores were 48.8 and 46.0, respectively [11]. In three other studies with 89%, 50% and 80% patients with NYHA stage III or IV, the mean MLHFQ scores were 49.3, 51.8, and 44.7, respectively [12,13,23]. Our patients will probably be older, with a better quality of life than the patients in all these studies because they are recruited in a primary care setting with NYHA stage I, II or III.

To our knowledge only one other cluster-randomised trial that measured the impact of a patient education programme by GPs has been published [23]. A total of 283 patients (mean = 76.3 years) were included: stage I – 1.8%; stage II – 7%; stage III – 38.9%; and stage IV – 50.5%. The mean MLHFQ score was 49.1 and 49.9 in the intervention and control groups, respectively.

The frequency of the visits in the ETIC trial, every 3 months, was similar to the standard of care; 87% of patients with heart failure meet their GP at least four times a year [38]. However, the educational aspects of the visits can be difficult for some of the GPs in the intervention group.

This study has limitations. The GP randomisation was done before the patient inclusions. The patients in the two groups might be different because the training received by the GPs in the intervention group may make them feel more competent and therefore, more inclined to include more severely ill patients. To avoid this bias, we could recruit randomised GPs after they had included their patients, using the ‘Zelen’ method [39]. Unfortunately, this has not been possible because the inclusion period lasts one year and the follow-up 19 months; regarding heart failure patient life expectancy, it would not be relevant [5].

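### Cumulative hospital days makes no allowance for follow-up ended by death, so longer survival alone raises the total; the death/HF-admission composite needs a single definition

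*Protocol article*

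**What the plan says.** Instruments and outcomes names as secondary outcomes "the cumulative number of all cause death or HF hospitalizations and the cumulative number of days of hospitalisation". Mortality stands there as an outcome of its own ("all-cause and heart-failure-associated mortality"). No denominator, time at risk or scoring rule for patients who die accompanies the two cumulative outcomes. When a visit is missed, "the reason is identified and categorised as follows: lost-to-follow-up; death; unable to attend for another reason", so death is recorded separately from loss to follow-up, but no consequence for the totals is drawn.

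The objectives at the end of the Background word the composite differently, as "the cumulative number of all cause death and HF hospitalisations". They close with "treatment for a follow-up period of 19 months".

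The Statistical analysis section says that the secondary analyses "will compare deaths (overall and due to heart failure) using Kaplan-Meier estimation and the Cox proportional-hazards regression model". Hospitalisations are assigned to the longitudinal random-effects models set out for quality of life. Missing data, for GPs and patients alike, are left to one general method. Neither the cumulative days nor the composite is mentioned by name, and no exposure or terminal-event term appears.

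The Background reports from a meta-analysis that disease management "leads to a significant reduction in mortality (odds-ratio (OR) = 0.80". The same sentence gives odds ratios of 0.76 for heart-failure admission and 0.58 for admission for any illness.

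**The concern.** Hospital days can only accumulate while a patient is alive. A total that ignores time alive therefore mixes two things: how much hospital care patients need per month of life, and how many months they live. More of the second raises the total even when the first has not changed, so an effect that is good for patients moves the outcome in the unfavourable direction.

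Deaths during follow-up are foreseeable here. The Discussion expects a mean age comparable to the 78.5 years of an Italian primary care study. In explaining why GPs could not be randomised after including their patients, it also says that "regarding heart failure patient life expectancy, it would not be relevant". That remark concerns recruitment order and not these outcomes, but it shows that the authors regard survival as limited on the trial's time scale.

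The Discussion concedes that power for secondary outcomes may be low and says interpretation will look at effect size and not only at significance. A distorted point estimate matters in that setting. The separate mortality comparison lets a reader notice a divergence, but it does not correct the hospital-day estimate.

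**Working it through.** The article gives no figure for either outcome, so there is none to reproduce.

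**Inputs.** From the article: 19 months of follow-up; mortality odds ratio 0.80. Assumed, because the article gives no values: control mortality p of 10%, 20% or 30% by month 19; 0.5 hospital day per month alive in both arms; constant hazard of death. The percentage excess below does not depend on the day rate.

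**Two patients.** With 19 × 30.4 = 578 days of follow-up:
- Death at month 2 outside hospital: 0 hospital days. Days alive and out of hospital: 2 × 30.4 = 61.
- Survival with one 10-day admission: 10 hospital days. Days alive and out of hospital: 578 − 10 = 568.

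The raw total ranks the death as the better result.

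**Two arms.** Intervention mortality q = 0.8o/(1 + 0.8o), with o = p/(1 − p). Mean months alive L(p) = 19p/(−ln(1 − p)). For p = 0.20: o = 0.25, q = 0.20/1.20 = 0.167, L(p) = 3.8/0.2231 = 17.03, L(q) = 3.167/0.1823 = 17.37. Expected hospital days = 0.5 × L.

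| Mortality, control / intervention | Months alive | Hospital days | Excess |
|---|---|---|---|
| 10% / 8.2% | 18.03 / 18.21 | 9.02 / 9.11 | +1.0% |
| 20% / 16.7% | 17.03 / 17.37 | 8.51 / 8.68 | +2.0% |
| 30% / 25.5% | 15.98 / 16.46 | 7.99 / 8.23 | +3.0% |

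Per month alive the arms are identical by construction, so the excess is entirely due to longer survival.

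**Against days alive and out of hospital.** Now spread deaths evenly over the 578 days and assume 10 hospital days per 578 days alive. The difference in days alive is 578(p − q)/2 = 5.3, 9.6 and 12.9. The difference in hospital days is that × 10/578 = +0.09, +0.17 and +0.22. Days alive and out of hospital then differ by +5.2, +9.5 and +12.7 in favour of the arm with fewer deaths, while raw hospital days point slightly the other way.

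**Deaths concentrated in the frail.** Assume all deaths fall in a frail 25% of patients. The others have 0.2 HF admissions per year, each admission lasts 10 days, and the frail have 0.6 to 4 admissions per year while alive. The excess is then 2.4% to 4.6% at 10% control mortality and 7.3% to 17% at 20%. For 20% and 0.6 per year, 3.56 against 3.82 days.

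**What would offset it.** A day rate while alive that is lower by 1 − 1/1.01 = 1% up to 1 − 1/1.03 = 3% cancels the excess in the table. At the 17% extreme, 1 − 1/1.17 = 15% is needed.

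**The composite.** Expected count = admission rate × months alive + probability of death. At 20% control mortality and 0.6 HF admissions per year (0.05 per month): control 0.05 × 17.03 + 0.200 = 1.051; intervention 0.05 × 17.37 + 0.167 = 1.035. The arm with fewer deaths still does better. The two are equal at a rate of 12(p − q)/(L(q) − L(p)) = 1.22, 1.18 and 1.13 admissions per patient-year for control mortality of 10%, 20% and 30%. In the frail scenario equality comes at 1.08 (10% mortality) or 0.77 (20%) per year within the frail quarter.

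**The case against.** **This is detail for the analysis plan.** An article condenses, and an offset or a terminal-event rule for a secondary outcome could sit in a document not shown. Part of this stands. If days were modelled by visit interval, visits after death would be missing and not zero, and the raw-total bias would give way to an implicit assumption about outcomes after death. But the article does more than stay silent. It fixes the outcome itself as a total and names the model family for hospitalisations, and neither allows for death.

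**The effect is small.** In the homogeneous scenarios it is 0.1 to 0.2 day on roughly 8 to 9, for an outcome already conceded to have low power. That is fair and limits the weight of the point. The larger figures need deaths to cluster in often-admitted patients, which is an assumption.

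**A reader might infer that a real benefit would appear as harm.** The documents do not support that as an expectation. The sentence that gives the mortality odds ratio also gives reduced odds of hospitalisation (0.76 and 0.58). If the intervention lowered the admission rate by more than the few per cent shown above, hospital days would still fall, only by less than they should. Nor does the protocol project a survival benefit for this trial. It says that hospital-based and outpatient-based programmes generalise poorly to primary care and that multidisciplinary ones are probably more effective.

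**A reader might extend the same charge to the composite.** There death is itself an event, so an early death beats only a survivor with two or more HF admissions. Reversal needs admission rates that the documents neither state nor exclude. The wording with *or* can also be read as a first-event composite, which would not have the problem.

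**Total days validly describes hospital burden.** It does, as a resource measure. It is a poor measure of patient benefit when survival may differ between arms.

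**Conclusion.** The point holds for cumulative hospital days. As stated, the outcome makes no allowance for follow-up ended by death: death contributes nothing, and longer survival alone raises the total. The size is about 1% to 3% with the cited odds ratio of 0.80 and assumed control mortality of 10% to 30%. It is more, up to 17% in the scenarios tried, if deaths concentrate in frail patients who are often admitted. All mortality and admission rates are assumptions; only the odds ratio and the 19 months come from the article. The consequence is dilution of a benefit, with a change of sign only where the admission rate while alive is essentially unchanged.

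For the composite, no reversal is claimed at low admission rates. What remains is an unsettled definition: the objectives join the two components with *and*, the outcome list with *or*, and neither says whether events are counted or the first one is timed. Both outcomes are secondary, so the primary conclusion of the trial is not affected.

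**What to change.** 1. Make days alive and out of hospital from inclusion to month 19 (578 minus days dead minus days in hospital) the replacement for cumulative hospital days, or the main measure with cumulative days reported beside it. If the raw total is kept, show mean time alive by arm next to it.
2. Define the death/HF-admission composite once, in both the objectives and the outcome list: either time to first event, or a recurrent-event rate per time at risk with death as the terminal event.
3. In the statistical section, name both outcomes and state that death is handled separately from dropout, with a rule for patients lost to follow-up while alive.

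The cost is a few sentences and one derived variable. Kaplan-Meier and Cox analyses already require dates of death, and days in hospital are already an outcome, so patients followed to death or month 19 need no new data. The small downside is less direct comparison with studies that report raw hospital days; keeping that total as a descriptive line largely removes it.

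### Patient adherence is measured at two times only, yet it is assigned to a random slope-and-intercept model that this schedule cannot fully identify

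*Protocol article*

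**What the plan says.** Under Instruments and outcomes, the secondary outcomes include "adherence with therapy; evolution of NYHA heart failure stage; evolution of treatment". Patient adherence is self-reported on a "self-administrated questionnaire (validated in French) at baseline and at the end of follow-up period". The secondary objectives in the Background put the end of follow-up at month 19 ("treatment for a follow-up period of 19 months"). Quality of life, by contrast, is collected at baseline and three times afterwards, at months 7, 13 and 19.

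Under Statistical analysis, the secondary comparisons cover "NYHA stage, treatment, adherence, weight and obesity between the groups with longitudinal random-effects models described previously". The only longitudinal model described before that sentence is a hierarchical linear regression with "random-effects levels for practice, individuals within practices and repeated measurements per individual (slope and intercept"). It estimates "effects of the intervention on SF-36 and MLHFQ scores for the post-baseline time points". On the fixed part the section adds: "These models will include an interaction factor between both the randomisation group and the particular time point". Its covariate list contains one baseline outcome score, SF-36, together with demographic and clinical variables. No other model is given for adherence.

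**The concern.** The model suits the quality-of-life schedule, but the cross-reference carries it over to an outcome with a different schedule. With one post-baseline value per patient there are no repeated measurements to model. Time does not vary, so the interaction repeats the group term. The slope has no information behind it, and the patient intercept cannot be told apart from residual error. The covariate list also has no place for baseline adherence, so one of the two adherence measurements would go unused.

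Adherence is a declared secondary objective of an education trial. If its stated model cannot be fitted as written, the analysis actually reported will differ from the plan, and the article does not say in which direction.

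**Working it through.** The article states no figure on this point to reproduce. The check is whether the stated model is identified under each measurement schedule, taking it as linear with normal errors, as the section describes.

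**Inputs.** Adherence times: 0 and 19 months (Instruments and outcomes; Background). Post-baseline quality-of-life times: 7, 13 and 19 months (Instruments and outcomes). Model terms: Statistical analysis.

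**Parameters.** Fixed part: intercept, group, time (linear), group × time, so 4. Covariance part: practice variance *p*, patient intercept variance *a*, slope variance *b*, intercept–slope covariance *c*, residual variance *s*, so 5.

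**Moments.** For times *t* and *u*:
- variance of one value: p + a + 2tc + t²b + s
- covariance of two values from the same patient: p + a + (t+u)c + tu·b
- covariance between two patients of the same practice: p

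**One post-baseline value (t = 19).**
- Fixed part: the time column is 19 times the intercept and the interaction column is 19 times group, so the rank is 2 of 4. The intercept and the group difference remain estimable.
- Covariance part: only p and p + a + 38c + 361b + s are observed, so the rank is 2 of 5.

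**Baseline kept as an outcome (t = 0, 19).**
- Fixed part: 4 of 4, so group × time is estimable.
- Covariance part: the distinct moments are p; p + a + s; p + a + 19c; and p + a + 38c + 361b + s. That is 4 equations for 5 unknowns, so the rank is 4 of 5.
- Without the slope, the parameters are p, a and s, and the rank is 3 of 3.

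**Quality-of-life schedule (t = 7, 13, 19).** Rank 4 of 4 and 5 of 5.

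| Values modelled | Fixed (of 4) | Covariance (of 5) |
|---|---|---|
| Month 19 only | 2 | 2 |
| Months 0 and 19 | 4 | 4 |
| Months 7, 13, 19 | 4 | 5 |

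**What the missing rank means with two values.** Code time 0/1, hold the practice variance fixed, and compare two illustrative sets (a, b, c, s):
- 50, 30, 5, 40: variances 50 + 40 = 90 and 50 + 10 + 30 + 40 = 130; covariance 50 + 5 = 55.
- 60, 50, −5, 30: variances 60 + 30 = 90 and 60 − 10 + 50 + 30 = 130; covariance 60 − 5 = 55.

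Both give the same 2 × 2 covariance matrix. The generalised least squares estimate of group × time and its standard error depend on the parameters only through that matrix, so they are the same for both sets. Only the split of the variance is arbitrary.

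**Baseline adjustment.** Adjusting a final value for its own baseline removes about ρ² of the patient-level residual variance, where ρ is the correlation between the two. The article gives no ρ. For an assumed 0.4 to 0.6, the reduction is 0.4² = 16% to 0.6² = 36%.

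**The case against.** The strongest reply is that the cross-reference is shorthand. The post-baseline restriction and the slope-and-intercept wording stand in a sentence about SF-36 and MLHFQ. The secondary sentence then covers several unlike outcomes at once. Read literally, even weight would be adjusted for baseline SF-36. On this view the section names a class of mixed models and leaves the random terms and the baseline handling of each outcome to the analysis plan, which the Discussion mentions and which is not shown. This has force as an account of what was probably intended. It does not remove the conflict, because the sentence names adherence, points to one described model and offers no alternative.

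A second reply is that adherence might mean guideline adherence of treatment, which is assessed during follow-up as well. That is the less likely reading, since the listed outcome is adherence with therapy and treatment appears separately in the same sentence. If it were right, the patient questionnaire would have no stated longitudinal model.

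Several stronger conclusions are tempting, and the document does not support them:
- A reader might infer that the effect on adherence cannot be estimated at all. The group difference at month 19 is estimable even on the literal reading, and group × time is estimable once baseline is in the outcome vector.
- A reader might infer that the analyst must choose a model after seeing results. The redundancy follows from a schedule known in advance, and the statistician is to be blinded to allocation.
- A reader might take 16% to 36% as the plan's loss of precision. It rests on an assumed correlation, and it applies only if baseline adherence is really left out.

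**Conclusion.** The point holds as an inconsistency between the adherence schedule and its assigned model. Taken literally, the interaction, the random slope and a separate patient intercept are not estimable, and baseline adherence has no place in the model. On the more generous reading with baseline as an outcome, the treatment contrast is sound and only the slope, intercept and residual variances cannot be separated.

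The scope is one secondary outcome. The primary quality-of-life model is identified under its own schedule and is unaffected. The conclusion assumes that adherence in the analysis section means the patient questionnaire and that the model is linear with normal errors. It does not depend on the sample size or on any assumed correlation.

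**What to change.** Take adherence out of the list referred to the slope-and-intercept model and add one sentence. For example: end-of-follow-up patient adherence will be compared between groups with a mixed model (linear for the score, logistic if it is dichotomised) adjusted for baseline adherence and the listed covariates, with a random intercept for practice and no patient slope or time interaction.

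An equally valid alternative is a model of both time points with random intercepts for practice and patient, a group-by-time term and no random slope. Either will do, provided that one is named in advance. The same sentence should say that adherence here means the patient questionnaire.

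The cost is a wording change in the analysis section. Both adherence values are already scheduled, so no visit or data item is added.
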